## Introduction

Neoadjuvant chemoradiotherapy (nCRT) followed by total mesorectal excision (TME) has been the standard treatment for locally advanced rectal cancer, significantly reducing local recurrence rates [1–4], particularly in cases with threatened mesorectal fascia (MRF) or a positive circumferential resection margin (CRM) [5,6]. However, despite its oncologic benefits, nCRT is associated with considerable morbidity, including bowel dysfunction, fecal incontinence, and sexual dysfunction, which can severely impact patients’ quality of life (QoL) [2,3,7]. Additionally, with advancements in rectal cancer surgery, the necessity of nCRT for all locally advanced rectal cancer cases has been increasingly debated.

Several studies, including OCUM, MERCURY, and QuickSilver, have investigated more selective approaches to nCRT to minimize overtreatment while maintaining oncologic safety [8–10]. These studies have demonstrated that MRI-predicted negative CRM strongly indicates favorable oncologic outcomes, allowing for primary surgery without nCRT in appropriately selected patients. The OCUM trial, in particular, showed that patients with magnetic resonance imaging (MRI)-negative CRM undergoing upfront TME had an acceptably low local recurrence rate (<10%) at five years [8]. The MERCURY trial further validated MRI as a reliable tool for preoperative risk stratification, demonstrating a high accuracy in predicting negative CRM and a low risk of local recurrence in MRI-negative patients [9]. Despite these promising results, the optimal selection criteria for omitting nCRT remain a subject of ongoing research.

Current European guidelines, including those from the European Society for Medical Oncology (ESMO), advocate a risk-adapted approach to nCRT. According to ESMO, patients with cT3a/b rectal tumors located above the levator muscles, without CRM involvement or extramural vascular invasion, are considered to have a low risk of local recurrence and may be candidates for upfront surgery without nCRT [11]. This contrasts with North American guidelines, which still recommend routine nCRT for stage II and III rectal cancers [12]. However, given that modern surgical techniques have significantly reduced the risk of CRM positivity and local recurrence, a more selective approach to nCRT may be warranted.

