### Statistical methods

During the study, missing data analyses and data quality assessments will be actively conducted, and measures to prevent data loss and enhance data quality will be implemented as appropriate. All statistical analyses will be conducted by experts from the TSCRS Biostatistics and Bioinformatics Analysis Unit using SPSS (SPSS Inc, Chicago, IL) software packages.

Multivariable regression analyses will be conducted to evaluate the effect of treatment strategy (direct TME vs. nCRT followed by TME) on the primary and secondary outcomes. The following covariates will be included in the models based on clinical relevance and literature review: age, sex, clinical T stage (cT2 vs. cT3), clinical N stage (N0 vs. N+), tumor differentiation, regimens of neoadjuvant treatment (long-course CRT, short-course RT, TNT with long or short-course RT), interval between neoadjuvant RT/CT and surgery, comorbidities (e.g., Charlson Comorbidity Index), performance status, postoperative complications (Clavien-Dindo), tumor histology, pathologic TME quality (pathologic completeness of the mesorectum), and center effect (as a random effect if appropriate).

For time-to-event outcomes such as disease-free survival (DFS) and overall survival (OS), Cox proportional hazards regression models will be used to estimate hazard ratios and 95% confidence intervals. The proportional hazards assumption will be tested using Schoenfeld residuals.

To address potential selection bias due to the non-randomized design, propensity score methods will be applied. Specifically, propensity scores for receipt of nCRT (vs. direct TME) will be estimated using logistic regression including the aforementioned covariates. The primary analysis will adjust for the propensity score as a covariate in the Cox model. Sensitivity analyses will be conducted using propensity score matching (1:1 nearest neighbor matching without replacement) and inverse probability of treatment weighting (IPTW) to ensure the robustness of results.

Patients lacking the main data specified in the inclusion and exclusion criteria, demographic data, or follow-up data related to the primary endpoint will be completely excluded from the study. Patients with missing data from other variables or secondary endpoints will only be excluded from those specific analyses, and secondary endpoints will be evaluated using data from patients with complete datasets.

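### The propensity score includes neoadjuvant regimen and treatment-to-surgery interval, which exist only in the nCRT group, so the adjusted comparison cannot be estimated as written

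*Protocol article*

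**What the plan says.** The Statistical methods section gives a single covariate list for the multivariable models of the primary and secondary outcomes: "The following covariates will be included in the models based on clinical relevance and literature review". Besides baseline items (age, sex, cT, cN, differentiation, comorbidity, performance status, centre), the list contains "regimens of neoadjuvant treatment (long-course CRT, short-course RT, TNT with long or short-course RT), interval between neoadjuvant RT/CT and surgery" and "postoperative complications (Clavien-Dindo), tumor histology, pathologic TME quality (pathologic completeness of the mesorectum".

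The same section then uses this list for the propensity score: "propensity scores for receipt of nCRT (vs. direct TME) will be estimated using logistic regression including the aforementioned covariates". No listed variable is exempted. The score enters the primary analysis as a covariate in a Cox model. The two sensitivity analyses are 1:1 nearest-neighbour matching without replacement and IPTW.

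The Interventions section defines the direct TME group as patients who have no neoadjuvant treatment before surgery. The missing-data rule in Statistical methods removes a patient with a missing value in any other variable from the analyses that use that variable.

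**The concern.** A propensity score is the probability of receiving a treatment given what was known when the choice was made. Two of the listed variables are consequences of the choice itself: a patient has a neoadjuvant regimen and an interval after it only if nCRT was given. A model that predicts nCRT from the details of nCRT measures nothing about selection.

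The comparison is non-randomised, and the article names propensity methods as its means of addressing selection bias. The primary analysis and both sensitivity analyses share the same score, so the sensitivity analyses cannot reveal or rescue a failure of the primary one. The separate multivariable outcome model uses the same list.

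Two further variables, complications and TME quality, become known only after surgery. They raise a different and milder problem, which is kept apart below.

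**Working it through.** The plan gives no figure for this point. The check is a logical one, with a simulation as illustration.

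**Inputs.** Covariate list, propensity model, primary and sensitivity analyses, missing-data rule: Statistical methods. Group definitions: Interventions. Total of 436 patients: Sample size and recruitment. Let T = 1 for nCRT and 0 for direct TME, and let e be the fitted score.

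**1. Regimen and interval coded as none or 0 for direct TME.** Every nCRT patient has a regimen and a positive interval; every direct TME patient has neither. Patients who do not complete neoadjuvant therapy stay in the nCRT group (Exclusion criteria), so they do not blur the boundary. The logistic model separates completely, no finite maximum-likelihood estimate exists, and e goes to 1 when T = 1 and to 0 when T = 0. It follows that:
- *Primary Cox model.* The linear predictor is βT + γe. With e = T it becomes (β + γ)T, so only the sum is identified and the treatment effect β is not.
- *IPTW.* Weights are 1/e = 1/1 = 1 for nCRT and 1/(1 − e) = 1/(1 − 0) = 1 for direct TME. The weighted comparison is the crude one.
- *Matching.* Any nCRT patient and any direct TME patient differ by 1 − 0 = 1 on the score, so there is no common support and no pair is closer than another.

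**2. Multivariable outcome model.** The list names long-course CRT, short-course RT and TNT. With indicators R1, R2 and R3, T = R1 + R2 + R3 for every patient. An example design matrix has an intercept (1), treatment (1), three baseline covariates (3), three regimen indicators (3), complications (1) and TME quality (1): 1 + 1 + 3 + 3 + 1 + 1 = 10 columns. Its rank is 9, so the treatment effect is not identifiable. Splitting TNT by type of radiotherapy adds an indicator but leaves the identity intact.

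**3. Regimen and interval treated as missing for direct TME.** The complete-case rule then removes every direct TME patient from the propensity model, and there is nothing left to compare.

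**4. Complications and TME quality.** Both exist in both groups, so they cause no separation. They follow treatment and may be affected by it. Adjusting for them can remove part of the treatment effect or introduce bias.

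**5. Simulation.** 300 data sets of 436 patients, with assumed covariate distributions, regimen and interval coded 0 for direct TME, and a very small ridge term so that the separated model returns numbers. Medians:

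| Covariates in the score | Lowest score, nCRT | Highest score, direct TME | Common support |
|---|---|---|---|
| Pre-treatment only | 0.25 | 0.72 | about 99% |
| Plus complications and TME quality | 0.21 | 0.83 | about 98% |
| Full set with regimen and interval | 1.000 | 0.000 | 0% |

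With the full set, the score and treatment had a correlation of about 1.0 in the primary Cox model, and the median standard error of the treatment log hazard ratio exceeded 500,000. With pre-treatment covariates only it was about 0.20.

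**The case against.** The strongest reply is that the failure would be conspicuous. The logistic model would not converge, the score distributions would not overlap, and an analyst would drop the offending variables. Software might also drop one redundant column of the outcome model and print a coefficient. This is fair: a silently wrong result is less likely than a visible breakdown. But the covariate set of the primary analysis would then be chosen after outcomes have been seen, in a study whose six-monthly interim analyses are run by steering-committee members without an independent committee. A coefficient left after automatic column dropping would also no longer be the effect of nCRT as a whole against direct TME.

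It may also be said that a condensed article leaves covariate detail to an analysis plan. That does not apply here, because the article names the variables and says that the score includes them. The Limitations section concedes residual confounding in general terms but does not touch this problem.

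Other objections do limit the point. A reader might infer more than the documents support in five ways:
- *All four post-treatment variables break the score.* They do not. With complications and TME quality alone, overlap stays at about 98%.
- *The resulting bias favours a finding of no difference.* No direction is shown. If nCRT raised complications and complications worsened DFS, adjusting for them would remove a harm of nCRT and make it look better.
- *The propensity score is the only protection against confounding.* Eligibility already excludes MRF involvement, EMVI and pathological lateral nodes, and multivariable models are planned, although these share the faulty list.
- *The plan intends to discard the direct TME group.* The article states no coding, and a value that does not apply need not count as missing. Step 3 is one of two possible consequences.
- *Leaving out tumour height and cT3 substage is an error.* The Introduction cites guideline criteria that mention "patients with cT3a/b rectal tumors located above the levator muscles", but nothing says that these drive treatment choice within this restricted mid-rectal cohort, and the list of database variables (S2 File) is not shown.

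**Conclusion.** The point holds, and the text should be corrected before the analysis is fixed. As written, including "regimens of neoadjuvant treatment (long-course CRT, short-course RT, TNT with long or short-course RT" and "interval between neoadjuvant RT/CT and surgery" in the score makes the primary Cox analysis non-estimable, turns IPTW into the crude comparison and leaves matching without common support. Including the regimen in the outcome model makes the treatment effect there non-identifiable. This follows from the definitions of the groups and variables. The simulated figures only illustrate it, and they depend on assumed distributions.

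The inclusion of "postoperative complications (Clavien-Dindo") and TME quality is a secondary fault: the estimate can still be computed, but it is no longer the total effect of the treatment strategy, and its bias may go either way. Differentiation and histology are not counted as faults. They are sound if taken from the pre-treatment biopsy, and the article does not state the source.

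**What to change.** Split the covariate list.

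- **Propensity score and primary adjusted outcome model:** only variables known before the treatment decision, namely age, sex, cT, cN, differentiation and histology from the biopsy, comorbidity, performance status and centre.
- **Regimen and treatment-to-surgery interval:** only in analyses within the nCRT group. The Restaging section lets between-centre variation in restaging enter the regression models; the same rule should cover it, because restaging is recorded only after neoadjuvant treatment.
- **Complications and TME quality:** report as outcomes, or use in a separate mediation analysis.

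As an optional improvement, add tumour height and cT3 substage from the baseline MRI if the database records them.

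The cost is a rewording of one paragraph in Statistical methods. No sample-size figure changes, and no new patients, visits or procedures are needed. The article reports that recruitment had not begun when it was written, so the change could be made before any outcome is known.

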### Main question

H_0_: There is no difference in 3-year disease-free survival between direct TME and TME following nCRT in patients with mid-rectal cancer (cT2N+ and cT3Nx) without high-risk MRI findings regarding local recurrence.

H_1_: Direct TME is associated with worse 3-year disease-free survival compared to TME following nCRT In patients with mid-rectal cancer (cT2N+ and cT3Nx) without without high-risk MRI findings regarding local recurrence.

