### Interventions

The standard of care for the treatment of locally advanced rectal cancer is TME. In patients with cT2N+, cT3N0, and cT3N+ mid-rectal tumors, the administration of nCRT, as well as the direct TME, are both considered guideline-concordant standard treatment approaches and are widely practiced [11,12]. In this study, data from patients undergoing TME as part of routine medical care will be collected prospectively. No additional interventions, treatments and follow-up protocols outside of standard care will be implemented. At the end of the study, patients will be categorized into two groups based on whether they received nCRT and the two groups will be compared in terms of primary and secondary endpoints. No treatment or monitoring protocols differing from routine practice will be proposed for patients or surgeons in the study. The natural prognosis of the treatment arms will be observed.

All the patients undergoing TME described as a precise dissection of the rectum along with the surrounding mesorectal tissue and all pararectal lymph nodes are eligible for the study [13].

**Direct TME Group:** Patients who undergo direct TME without neoadjuvant treatment.

**nCRT Group:** Patients who receive nCRT prior to TME.

Neoadjuvan CRT treatments include all conventional chemoradiotherapy regimens or total neoadjuvant chemoradiotherapy regimens (standard short or long course radiation and/or any standard chemotherapy regimen) described in European and American guidelines [11,12]. The details of radiotherapy and chemotherapy treatments will be recorded, including dosage, frequency, duration, complications, completion status, and the waiting period between treatments. Routine follow-up information for all patients including morbidity, radiologic assessments, recurrence, mortality be recorded in the database for the first five years post-surgery. Patient-reported quality of life scales will be recorded at baseline (prior to the initiation of treatment) and subsequently at 1, 3, and 5 years.

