### Outcomes

#### Primary outcome measure.

3-year DFS: The proportion of patients who remain free of disease recurrence (local or distant) three years after surgical intervention. DFS will be assessed through clinical evaluations, imaging studies, and pathology reports at regular follow-up intervals.

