### Sample size and recruitment

The literature reports a mean 3-year disease-free survival rate of 75–85% for the sample to be included in the study [16]. For patients with mid-rectal tumors (cT2N+ and cT3N0) without high risk MRI findings, the 3-year disease-free survival rate was estimated to be 80% for both direct TME and TME following neoadjuvant chemoradiotherapy. Under these conditions, with α = 0.05 (95% confidence interval) and 80% power, the power analysis indicated that a total of 396 patients (1:1 ratio) would be required. Considering a 10% dropout rate, it is planned to include 218 patients in each group, for a total of 436 patients.

According to data from the Turkish Ministry of Health, General Directorate of Public Health, a total of 24,312 patients were diagnosed with rectal cancer between 2020 and 2024, of whom 17,896 underwent surgery (https://hsgm.saglik.gov.tr/tr/kanser.html). Since this study will be conducted nationally under the sponsorship of the main society of Turkish colorectal surgeons TSCRS, we anticipate reaching the targeted patient number within five years from the start of the study. To achieve this goal, TSCRS will utilize various channels, including mailing, social media, and its website, to announce the study and inform surgeons about the protocol.

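### The endpoint, hypotheses and sample size concern the 3-year DFS proportion, but the primary analysis is a Cox hazard ratio with no stated horizon, so the stated 80% power does not describe it

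*Protocol article*

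**What the plan says.** Four parts of the protocol article speak of DFS at a fixed time.

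- Primary outcome measure: "The proportion of patients who remain free of disease recurrence (local or distant) three years after surgical intervention".
- Main question, null hypothesis: "There is no difference in 3-year disease-free survival between direct TME and TME following nCRT".
- Main question, alternative: "Direct TME is associated with worse 3-year disease-free survival compared to TME following nCRT".
- Sample size and recruitment: "the 3-year disease-free survival rate was estimated to be 80% for both direct TME and TME following neoadjuvant chemoradiotherapy". With α = 0.05 and 80% power this leads to 396 patients in a 1:1 ratio, raised to 436 for dropout. The section gives no hazard ratio, event count or follow-up pattern.

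Statistical methods then assigns DFS to Cox models that estimate hazard ratios, and states: "The primary analysis will adjust for the propensity score as a covariate in the Cox model". It gives no cut-off at 3 years or at any other time. Under Interventions, follow-up information is to be "recorded in the database for the first five years post-surgery". On the model assumption the article says only: "The proportional hazards assumption will be tested using Schoenfeld residuals". Propensity matching and inverse probability weighting (IPTW) appear as sensitivity analyses, with no effect measure attached.

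**The concern.** A hazard ratio and a difference in 3-year proportions are different quantities, and neither the limit nor the power of one carries over to the other. A limit in percentage points has no fixed hazard-ratio equivalent, and a Cox test draws its power from the number of events, which depends on how long patients are followed.

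As written, the analysis labelled primary does not deliver the quantity in the endpoint definition, and readers cannot tell what power it has. If hazards are not proportional, a hazard ratio that averages over follow-up beyond 36 months can also overstate or understate the 3-year difference. This matters because the result is meant to inform whether nCRT can be omitted.

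**Working it through.** **Inputs.** From Sample size and recruitment: 80% DFS at 3 years in both groups, α = 0.05, 80% power, 396 patients, and a literature range of 75–85%. Assumed, because the article states neither: a 10-point limit and a one-sided 5% level. The only 10% DFS difference in the article is the threshold for terminating the study. Also assumed: exponential DFS, equal groups and no loss from covariate adjustment.

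**1. The plan's own figure.** For a non-inferiority comparison of two proportions, n per group = (1.645 + 0.842)² × 2 × 0.8 × 0.2 / 0.10² = 197.8, so 198 per group and 396 in total. This matches exactly. At one-sided 2.5% the same formula gives 252 per group (504). With equal rates and no limit, no sample size can be computed. A two-sided superiority test of 80% against 90% gives 398, but contradicts the stated 80% in both groups; it too is a comparison of proportions.

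**2. The same limit as a hazard ratio.** HR = ln(p − 0.10) / ln(p), where p is 3-year DFS.
- p = 75%: ln 0.65 / ln 0.75 = 1.50
- p = 80%: ln 0.70 / ln 0.80 = 1.598, with logarithm 0.469
- p = 85%: ln 0.75 / ln 0.85 = 1.77

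So 10 points correspond to anything from 1.50 to 1.77 within the article's own DFS range.

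**3. Power of the Cox analysis** (true HR 1, limit 1.598, 396 patients). Power = Φ(0.469 × √events / 2 − 1.645). The hazard is λ = −ln 0.80 / 3 = 0.0744 per year.

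| Horizon | Events | Power, one-sided 5% |
|---|---|---|
| Censored at 36 months | 396 × 0.20 = 79.2 | 67% |
| End of uniform five-year accrual | 396 × [1 − (1 − e^(−5λ)) / (5λ)] = 65.3 | 60% |
| Every patient followed five years | 396 × (1 − e^(−5λ)) = 123.0 | 83% |

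80% power needs 4 × 6.183 / 0.469² ≈ 112.4, that is 113 events. With a two-sided 95% interval (1.96 for 1.645), power at 36 months is 55%. A simulation of 4,000 trials censored at 36 months gave 67.6% for Cox and 79.6% for the Kaplan-Meier difference.

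**4. Power of the 3-year difference.** The standard error with 198 per group is √(2 × 0.16 / 198) = 0.0402, and 0.10 / 0.0402 = 2.487. Power is Φ(2.487 − 1.645) = 80% at one-sided 5%, and Φ(2.487 − 1.960) = 70% with a two-sided 95% interval. Both assume that all 396 patients are followed to 36 months.

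**The case against.** Cox regression is the usual model for DFS, the article condenses a fuller plan, and a statistical analysis plan may settle the details. Several parts of this objection stand.

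- **Power.** A reader might infer that the Cox analysis is simply underpowered. The documents do not support that: power is below 80% at 36 months and at the end of accrual, but about 83% if all patients are followed five years. The supportable statement is that 80% is not the power of this analysis.
- **Horizon.** A reader might infer that the model runs over all available follow-up. The article does not say so. Since 5-year DFS is a separate secondary outcome, a cut at 3 years is also a natural reading. Even with that cut, the estimate remains a hazard ratio, with about 67% power.
- **Other analyses.** Regression, matching or IPTW could be made to yield an adjusted 3-year difference. The article names none of them for that purpose, so such an estimate is unnamed rather than ruled out.
- **Limit.** The article fixes no non-inferiority limit, and its written null of no difference can be tested with HR = 1. The power figures therefore depend on an assumed limit.
- **Non-proportional hazards.** A reader might infer that a 10-point deficit at 3 years would readily pass. That needs an extreme case. With 80% against 70% at 3 years and 66% in both groups at five, the hazard ratio must reverse from 1.60 to 0.31 at year 3. Nothing in the documents supports such a pattern, and the planned residual test would usually flag it. The article states no consequence of a failed test, which a statistical analysis plan may supply.

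The mismatch itself remains. The article names its primary analysis, and that analysis is on a different scale from the endpoint and sample size in the same document.

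**Conclusion.** The point holds. The endpoint, hypotheses and sample size are on the 3-year DFS scale; the primary analysis is a hazard ratio without a horizon, and no adjusted 3-year estimate is named. The stated 80% belongs to a two-proportion comparison. For the Cox analysis the figure is about 67% at 36 months, and ranges from 60% to 83% over the follow-up patterns examined. These figures rest on the 10-point limit, one-sided 5%, 80% DFS in both groups, exponential DFS, 396 patients split equally, and no loss from adjustment. The mismatch of scale rests on none of these assumptions. Misstatement of the 3-year difference under non-proportional hazards is a possibility, not a demonstrated result.

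**What to change.** Name the propensity-adjusted difference in 3-year DFS, with its confidence interval, as the primary estimate. It can come from IPTW-weighted Kaplan-Meier curves or from standardised survival at 36 months. Keep the Cox hazard ratio, censored at 36 months, as supportive.

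State the limit in percentage points and a confidence level that matches the sample size. A one-sided 5% test (two-sided 90% interval) keeps 80% power before any loss from adjustment. If a two-sided 95% interval is preferred, restate power as about 70% with 198 per group.

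If the Cox model stays primary, state its horizon and express the limit as a hazard ratio. Then restate power for that horizon: at 36 months, about 67% at one-sided 5%, or 55% with a two-sided 95% interval.

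The cost is analysis wording. The change adds no patients and needs no data beyond the 36-month follow-up that the endpoint already requires. Choosing a two-sided 95% interval while holding 80% power would instead need 504 patients before dropout.
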